##### Overview

The following measures were administered in the order shown in Figure 3. All questions were presented on separate pages of the questionnaire. Participants were not able to go back or review their previous responses, except within each of the psychosocial item sections.

##### Screening History

Participants were asked when they last had a Pap test to assess their screening group: (1) within the past year, (2) within the past 1 to 3 years (adequately screened group), (3) >3 years ago, or (4) never (underscreened group). Then, the participants who reported receiving at least one previous Pap test were asked whether they had ever received an abnormal test result. In addition, given the study’s timing in the fall of 2021, participants who reported receiving a Pap test >3 years ago were asked whether the COVID-19 pandemic had prevented them from receiving a Pap test, as cervical cancer screening was paused in some provinces and territories during parts of the pandemic.

##### Sociodemographics

A total of 4 items used dichotomous response option (yes or no) to measure identification as visible minority [77]; influence of religious or spiritual beliefs on health decisions; living in Canada for ≥10 years; and completion of a trade certificate or diploma, college degree, or university degree. Self-reported ethnic origin was measured with 1 item using the 9 response options recommended by Statistics Canada [78]. We used multiple validated response options to measure gender identity [79]. In addition, household income, employment status, province or territory of residence, and travel time between one’s home and a health care office or clinic were measured.

##### Cervical Cancer–Related Health Behaviors and Risk Factors

Participants answered the following items: self-reported health (from very poor [1] to excellent [6]) [80], use of oral birth control pills for ≥5 years (yes or no), number of children given birth to (0 to ≥10), smoking history (current smoker, smoked in the past, or never smoked), vaccination with at least one dose of an HPV vaccine (yes or no or don’t know), having a family physician (yes or no), height, weight, previous diagnosis of sexually transmitted infection (yes or no), number of lifetime sexual partners, and age of sexual debut.

##### Psychosocial Items for Scale Development

Participants were presented with all items selected as part of phase 1A For the knowledge items, participants responded to each item with *true*, *false*, or *I don’t know*. For attitudes and beliefs items, participants responded to each statement on a 7-point Likert scale ranging from strongly disagree (1) to strongly agree (7). Item presentation was randomized within each section for each participant to mitigate order bias.

##### HPV Testing and Self-sampling Intentions

Using the Precaution Adoption Process Model (PAPM) [81], women selected their current decision-making stage regarding the proposed screening method (HPV testing or self-sampling using the HPV test) from five options: (1) unengaged in the decision to be screened with the HPV test or self-sampling, (2) undecided about whether to be screened with the HPV test or self-sampling, (3) decided not to be screened with the HPV test or self-sampling, (4) decided to be screened with the HPV test or self-sampling, or (5) acted (already screened with the HPV test or self-sampling). A full description of the theoretical background and use of PAPM is provided in the *Study Design* section of study 2.

##### BWS for Screening Preferences

Following the orthogonal main effects design recommended by Aizaki and Fogarty [64] and using the R software packages, *DoE.base* [82] and *support.BWS2* [64], a full set of questions was developed for each of our 2 domains: screening intervals (domain A) and age of screening initiation (domain B). To examine preferences in domains with 4 attributes (ie, screening methods), each of which have 3 attribute levels (ie, screening interval options [domain A] and screening initiation options [domain B]), participants must answer 9 questions that contain the same number of randomly assigned combinations of attribute levels (corresponding to the defined attributes). Therefore, participants answered 18 items; 9 related to cervical cancer screening intervals and 9 related to age of initial screening. Items within each domain were presented randomly for each participant.

##### Preferences for Screening Information and Routine Screening

Using a drag-and-drop interface, participants ranked their preferred source of information from the following options: public health agency website, social media, and health care professional. A similar item was used to assess participants’ preferred type of health care practitioner to administer routine HPV testing among the following: family physician, gynecologist, nurse or nurse practitioner, and physician’s assistant.

##### Recruitment and Data Collection

Recruitment and survey programming were facilitated by Dynata, an international market research firm. Before administering the programmed questionnaire, the research team tested the survey using multiple permutations of response options to ensure its technical functionality and usability and made changes as necessary. Then, Dynata administered the survey to their large panel of Canadian residents who are recruited through *by-invitation-only* method, in which participants’ identities are validated by other partnered businesses to ensure response quality. Eligible participants were invited to complete a survey about *health and wellness* through several platforms, including emails, smartphone app notifications, and Dynata’s website, using a link that is unique to each potential participant. Before beginning the survey, participants’ IP address and unique identifier provided to them by Dynata were used to flag potential duplicate responses. Sample recruitment was conducted over 2 weeks in October 2021 and November 2021. Participants were compensated according to Dynata’s rewards and points system (eg, Amazon and Starbucks). Participants were required to complete all questions before continuing the survey to prevent missing data.

##### Sample Size

We calculated the minimum sample size for conducting factor analyses using the criteria recommended by Mundfrom et al [83], which include the expected ratio of variables to factors, level of communality, and agreement between the sample and population solutions (K). On the basis of ratio of variables to factors of 4 (for the 13 items reflecting attitudes and beliefs for sampling), low level of communality (ie, range 0.2-0.4), and excellent agreement between the sample and population solutions (ie, K=0.98), the minimum sample required was 500 (rounded up from 450). As our analytic plan includes conducting EFA and confirmatory factor analysis (CFA) on separate samples and considering that oversampling is needed to account for approximately 18% invalid and inattentive responses [84], the sample needed is 1220 observations, that is, (2 × 500 × 100) / 82 = 1219.

##### Data Cleaning

Direct and statistical data cleaning methods were used stepwise to identify potentially *inattentive* or *unmotivated* respondents in our final data set of completed questionnaire responses. In total, 2 attention check items were used in the survey: one within the items related to HPV test attitudes and beliefs scale and one in the items related to HPV self-sampling attitudes and beliefs. Following the instructed response design [84], each of these items asked participants to select a specific response choice from a Likert scale to verify attention (eg, “please select ‘strongly agree,’ for this question only”). Participants who responded correctly to at least one of these items were retained. Next, participants who *straight-lined* (ie, answered all items using the same response) were identified by calculating the variance in response for all the HPV testing attitudes and beliefs items. Participants who did not exhibit any variance in their responses across these items were excluded. Finally, among the remaining participants, those in the longest 2.5% and shortest 2.5% of the survey response times were excluded.

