**Figure 2 figure2:**
[figure not shown]
Flowchart of item sources.

At this stage, the focus was on the item’s underlying construct and not its wording. Reasons for rejecting items included the following: (1) duplicate of a factor already retained, (2) not applicable to Canadian context (eg, “There are resources in my community for low and no cost cervical cancer screenings” as Canada has a universal health care system [45]), (3) infrequent and isolated factor (eg, “I worry that tube contents may spoil or spill during transportation to doctor” [63]), and (4) not applicable to our project’s quantitative and survey methodology (eg, open-ended items such as “There are many warning signs and symptoms of cervical cancer. Please name as many as you can think of” [44]).

In total, of 781 items that were reviewed, 137 (17.5%) items were retained. Of these 137 items, 85 items were categorized for scale development: 14 for cervical cancer knowledge, 14 for HPV testing knowledge, 44 for attitudes and beliefs about HPV testing, and 13 for attitudes and beliefs about HPV self-sampling. These 85 items were reviewed and revised separately for clarity, consistency, and grade-8 reading level to account for different language and literacy levels. In addition, certain cervical cancer knowledge and HPV testing knowledge items were revised to achieve a balance of *true* and *false* items (ie, made negative or affirming by adding words such as *not*).

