### Strengths and Limitations

A major strength of this study is the rigorous and comprehensive process to develop psychometrically validated scales informed by theoretical frameworks. In addition, examination of the feasibility of the developed questionnaire through study 1 will ensure that the survey used in study 2 will be easy to understand and relevant to Canadian women. BWS presents an innovative approach to assess preferences that controls for biases observed in typical multiple-choice or ranking assessments of preferences. The use of PAPM to examine intentions toward HPV testing and self-sampling will provide a theoretically informed and nuanced understanding of women’s decision-making compared with other studies using continuous or binary measures. Using a market research polling firm will enable time-efficient and cost-efficient recruitment and data collection. Furthermore, the web-based survey methodology will prevent the issue of missing data. Quota-based sampling will allow us to recruit a nationally representative sample based on recent census data. Attention check items and data cleaning techniques will allow us to identify and exclude unmotivated or *careless* responders, ensuring that high-quality data will be collected and analyzed.

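### The Study 1 cleaning rule enforces neither an attention check nor a straight-lining test on the 13 self-sampling items, so flat answers to that block can enter its scale validation.

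*Protocol article*

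**What the plan says.** The Data Cleaning section (Study 1, Phase 1C) sets three steps in sequence.

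- **Attention checks.** There are two instructed-response items: "one within the items related to HPV test attitudes and beliefs scale and one in the items related to HPV self-sampling attitudes and beliefs". Passing one is enough: "Participants who responded correctly to at least one of these items were retained".
- **Straight-lining.** Flat responders are "identified by calculating the variance in response for all the HPV testing attitudes and beliefs items". Then: "Participants who did not exhibit any variance in their responses across these items were excluded".
- **Time.** Among those left, "those in the longest 2.5% and shortest 2.5% of the survey response times were excluded". This uses total survey time.

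The Item Selection section gives the block sizes: "44 for attitudes and beliefs about HPV testing" and "13 for attitudes and beliefs about HPV self-sampling". The scale-validation section plans exploratory and confirmatory factor analysis on random halves, a graded response model for attitude items, and Cronbach alpha per factor. Strengths and Limitations says that the attention checks and cleaning identify careless responders, "ensuring that high-quality data will be collected and analyzed".

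**The concern.** A check inside each block is useful only if each one is enforced. Under the either-check rule, failing the self-sampling check has no consequence for someone who passed the other. The variance test, which could have caught the same person, does not look at the self-sampling items.

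This block is also sensitive to contamination. The Study 1 sample size was set on these 13 items with an assumed communality of only 0.2 to 0.4. Where true inter-item correlations are weak, a small number of records with one repeated value can carry noticeable weight. Items retained here make up the shorter self-sampling scale used in Study 2.

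Disengagement partway through is plausible. The Questionnaire Feasibility section attributes 50 of 162 dropouts to the 44-item HPV attitudes section.

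**Working it through.** **1. The plan's own figures.** Sample size: (2 × 500 × 100) / 82 = 1219.5, rounded up to 1220, as stated. Retained: 1027 of 1230, so 203 were excluded (16.5%), close to the 18% allowed for. Each random half has about 1027 / 2 ≈ 513 respondents.

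**2. Tracing one respondent through the rules.**

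| Step | Behaviour | Outcome |
|---|---|---|
| Attention checks | Passes the HPV testing check, fails the self-sampling check | Kept (one of two) |
| Zero variance | Varies on the 44 HPV testing items | Kept |
| Self-sampling items | Same answer to all 13 | Not examined |
| Total time | Within the middle 95% | Kept |

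The respondent is retained, and no later step examines the block.

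**3. What the exclusion total reveals.** If the time trim removed exactly 5%, then 1027 / 0.95 ≈ 1081 respondents reached it. About 54 were lost to timing and 1230 − 1081 = 149 (12.1%) to the first two steps. This does not show how many retained respondents were flat on the self-sampling items. The article's text does not give that number, and the flow diagram (Figure 4) was not available to me.

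**4. Possible size, by simulation.** All of these are assumptions: 513 respondents, 13 seven-point items, communality 0.3 (the middle of the plan's range), factor number chosen by parallel analysis at the 95th percentile, and the contamination levels. At 2% and 6% contamination, about 10 and 31 of 513 respondents are flat.

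Three factors correlated 0.3 (the plan's ratio of 4 implies about three), at 0 / 2 / 5 / 10% flat responders:

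| Setting | Mean alpha per factor | Mean number of factors retained |
|---|---|---|
| Items worded one way, flat value spread over 1 to 7 | 0.63 / 0.66 / 0.71 / 0.75 | 3.0 / 3.0 / 3.0 / 2.5 |
| 6 of 13 items reverse-worded and rescored, flat value spread over 1 to 7 | 0.63 / 0.61 / 0.55 / 0.48 | 3.0 / 3.7 / 4.0 / 3.8 |
| All flat answers at the midpoint, either wording | 0.63 throughout | 3.0 throughout |

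In the first row the mean correlation between items of different factors rises from 0.09 to 0.26.

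Two factors of 7 and 6 items correlated −0.3, at 0 / 2 / 4 / 6%:

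| Flat values (SD of responses before rounding) | Alpha, first factor | Mean between-factor item correlation | Factors retained |
|---|---|---|---|
| Spread over 1 to 7 (SD 1.3) | 0.74 / 0.76 / 0.79 / 0.81 | −0.09 / −0.04 / +0.01 / +0.06 | 2 at every level |
| Only 1, 4 or 7 (SD 1.5) | 0.74 / 0.77 / 0.80 / 0.82 | −0.09 / −0.03 / +0.03 / +0.08 | 2 at every level |

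The rise in alpha runs from 0.76 − 0.74 = 0.02 at 2% to 0.82 − 0.74 = 0.08 at 6%. Combining only 1, 4 or 7 with SD 1.3 is harsher: alpha goes from 0.73 to 0.83 at 6%, a rise of 0.10. At 0.5% to 1% contamination the rise is about 0.01 to 0.02.

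**The case against.** The strongest reply is that the block is already screened. Failing both checks, straight-lining the 44 HPV testing items or falling in a time tail removes a respondent from every scale. The panel firm also validates identities and flags duplicates. Total exclusions came close to what was planned. Anyone who slips through was attentive enough to pass one check and vary on the long block. That stands: a reader might infer that the block is unprotected, but it has indirect protection and lacks only an enforced check of its own.

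Four stronger readings are also tempting, and the document does not support them.

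- **Reliability is inflated.** This depends on wording direction and on the values chosen. Balanced wording is described only for the knowledge items, and the direction of the self-sampling items is not given. Alpha could rise, fall or stay put.
- **Benefit and barrier factors merge.** In the two-factor setting, parallel analysis kept two factors at every level up to 6%. Some loss of factors appeared only in the three-factor, one-direction setting, mainly at 10%.
- **Study 2 repeats the rule.** The same-procedure sentence in the Study 2 design concerns data collection by the panel firm. The cleaning rule for Study 2 is not fixed either way.
- **Random responders get through easily.** A uniform random responder passes at least one check with probability 1 − (6/7)² = 0.265, but random answers are a different problem from flat ones.

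It is also fair that an all-neutral answer may be genuine. The Informative Statements section presumes that women know little about self-sampling.

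**Conclusion.** The gap in the rule follows directly from the text and needs no assumption: a respondent who failed the self-sampling check and gave one answer to all 13 items can be kept, and her data enter that scale's validation.

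The consequence is conditional. With 2% to 6% such respondents, off-centre flat values and one-direction wording, alpha within a factor rises by about 0.02 to 0.08 (0.10 under the harshest setting tried), and correlations between items of different factors shift upward. With reverse-worded items alpha can fall and a spurious extra factor can appear. With midpoint answers almost nothing changes. Since neither the number of such respondents nor the wording direction is stated, neither the sign nor the size of the bias can be fixed from the document. The case for acting is that the remedy is cheap and Study 1 analysis is described as ongoing; it does not rest on demonstrated harm.

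**What to change.** - For the self-sampling scale's factor analyses, graded response model and alpha, apply the zero-variance test to the 13 self-sampling items. Exclude at least those who also failed that block's attention check.
- Handle flat responders who passed the check as a separate sensitivity group. An all-neutral answer may be sincere, whereas a flat answer at the instructed value would pass by coincidence.
- Report exclusions by step, including how many failed only the self-sampling check and how many were flat on its items.
- Rerun with the current rule as a sensitivity analysis.
- State the same per-block rule for Study 2 before its data are cleaned.

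The cost is a few lines of code on data already held and a slightly smaller n for this one scale. Study 1 has 1027 − 1000 = 27 responses above the rounded requirement, and 1027 − 2 × 450 = 127 above the unrounded one.

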##### Data Analysis—Objective 1: Scale Validation

To evaluate dimensionality, we will conduct EFA and CFA separately for cervical cancer knowledge, HPV testing knowledge, and HPV testing and self-sampling attitudes and beliefs items. The final data set will be split randomly into 2 equal samples, and one sample will be used to conduct EFA and the other sample will be used to validate the factor structure using CFA. To select the optimal number of factors, we will use the parallel analysis approach and the syntax developed by O’Connor [85]. For items within each factor, we will use item response theory modeling; for binary data (knowledge items), we will use the 2-parameter logistic regression model that accounts for item difficulty and discriminant capacity; and for ordinal data (attitudes and beliefs items), we will use the graded response model that accounts for discriminant capacity and probability of selecting a certain Likert scale score (eg, strongly agree). Concurrently, we will examine how well each item measures the latent trait by plotting the item information against the latent construct ability. We aim to retain items that cover a wide range of difficulty and have high discriminant capacity and information value. To estimate the CFA model fit, we will use the fit indices and cutoff criteria recommended by Hooper et al [86]: (1) relative (normed) chi-square test (*χ*^2^/_df_=2 to 5) by Wheaton et al [87], (2) standardized root mean square residual (<0.8), (3) root mean square error approximation (<0.06), (4) comparative fit index (≥0.95), and (5) Tucker-Lewis index (≥0.95). To evaluate internal consistency for items loading onto each factor, Cronbach *α* will be calculated.

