### Objectives

The main objectives of study 1 (scale and questionnaire development) are as follows:

To develop psychometrically valid scales to assess women’s knowledge of cervical cancer and attitudes, beliefs, and knowledge about HPV testing and self-sampling.To evaluate the feasibility and acceptability of using a web-based survey related to Canadian women’s knowledge, attitudes, beliefs, and preferences about new HPV testing–based cervical cancer screening programs.

The main objectives of study 2 (expanded population-based survey of Canadian women) are as follows:

To estimate differences in HPV and cervical cancer screening knowledge and attitudes, beliefs, and preferences regarding HPV testing between women who are adequately screened and those who are underscreened.To estimate the multivariable associations between psychosocial factors (eg, knowledge, attitudes, beliefs, and sociodemographics) and intentions to use HPV testing and self-sampling in women who are adequately screened and those who are underscreened.

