##### Questionnaire Revisions and Translation

A draft version of the questionnaire was circulated to our team of coinvestigators and collaborators (globally based researchers and public health decision makers with expertise in HPV research, cervical cancer screening, epidemiology, oncology, psychometrics, behavior change, and health psychology theory) for review of accuracy of content and feedback. Their suggestions were reviewed and used to refine our questionnaire further (ie, item wording, informative statement content, and questionnaire structure). Then, this version was translated into French by a specialized translation firm, Asiatis, and verified by a native French-speaking member of the research team ([name]).

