#### Phase 1C: Data Collection and Psychometric Validation

##### Study Design

A cross-sectional web-based survey was administered from October 2021 to November 2021 to a national sample of Canadian women, aged 21 to 70 years, in English and French. Participants completed the questionnaire developed in phases 1A and 1B The survey design and preliminary results are reported according to Checklist for Reporting Results of Internet E-Surveys (CHERRIES; Multimedia Appendix 2) [76]. An electronic consent form describing the study investigators, study goals, procedure, expected survey length, and confidentiality was provided at the start of the survey. Then, the participants were asked whether they consented to taking part in the survey. By clicking on the icon that states they agree to participate, consent was implied, whereas if they declined, the survey was terminated. The information collected during the survey was completely anonymous.

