#### Study Design

A cross-sectional web-based survey will be administered in summer of 2022 to a nationally representative sample of Canadian women, aged 21 to 70 years, in English and French. The study population and inclusion criteria will be the same as those in study 1. Oversampling will be used to ensure that half of the sample is adequately screened and the other half is underscreened. Additional quotas will be used for the following factors: age, household income, and rural or urban residence (considering low cervical screening rates in rural Canada [7]) based on census data from Statistics Canada. Data collection will be conducted by Dynata, following the same procedure as that in study 2.

The questionnaire will follow the same structure and include the same sections as the survey detailed in study 1. Of the knowledge, attitudes, and beliefs items used for scale development in study 1, only those items retained after extensive psychometric analyses will be used in the study 2 questionnaire as part of the resulting shorter, validated scales. In addition, 2 previously validated measures, the extended HPV General Knowledge and HPV Vaccine Knowledge scales, will be added [69], given the relevance of HPV and HPV vaccination in cervical cancer. The measurement of the outcome variables (intentions to screen using the HPV test and self-sampling) is informed by PAPM [81], a categorical, stage-based model of health decision-making. As a binary, *yes or no* outcome limits accuracy, using a multistage model provides a more precise, nuanced understanding of women’s decision-making process that acknowledges the unique barriers associated with movement between each stage toward engaging with the behavior [90].

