#### Data Analysis

Corresponding to objective 1, we will conduct univariate analyses (means and proportions) for scale items (eg, knowledge and attitudes) and bivariate analyses (2-tailed *t* tests and chi-square tests) to estimate the differences between adequately screened women and underscreened women. We will calculate the effect size using Cohen *h* and Cohen *d* for proportions and continuous variables, respectively. Corresponding to objective 2, we will estimate the associations between psychosocial factors and intentions of HPV testing and self-sampling using multinomial logistic regression and model the log odds of PAPM stages (dependent variable) as a linear combination of the independent variables (eg, HPV testing knowledge and BWS preference scores). We will report odds ratios and 95% CIs of being in a PAPM stage versus the reference category (ie, unengaged) for each independent variable. Initially, we will conduct bivariate analyses to estimate the association between the outcome and independent variables. Then, independent variables showing significant associations (*P*<.10) will be entered simultaneously in the final model. We selected the following indices to report model fit: (1) Cox-Snell *R*^2^, (2) Cragg-Uhler *R*^2^, and (3) McFadden *R*^2^ [39,92]. We will use the Hausman-McFadden test to evaluate the final model for independence of irrelevant alternatives, which postulates that a person’s choice (ie, PAPM stage) is unchanged by other available choices (ie, fewer PAPM stages) [93]. Analyses will be conducted separately for underscreened women and adequately screened women. Analyses will be conducted using SPSS (IBM Corporation), R software (R Foundation for Statistical Computing), and STATA (StataCorp).

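### Items are validated and selected with both screening groups combined, and no check that they function alike in the two groups, yet study 2 compares those groups on the retained items

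*Protocol article*

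**What the plan says.** Study 1, Data Analysis—Objective 1: Scale Validation, opens with "To evaluate dimensionality, we will conduct EFA and CFA separately for cervical cancer knowledge" (the remaining item sets are then listed) and sets out the sequence in some detail: exploratory then confirmatory factor analysis, parallel analysis, a two-parameter logistic (2PL) model for knowledge items, a graded response model for attitude and belief items, item information, five fit indices with cutoffs, and Cronbach alpha. On the samples it says "The final data set will be split randomly into 2 equal samples". On item selection it says "We aim to retain items that cover a wide range of difficulty and have high discriminant capacity and information value". No grouping variable appears in any of these steps.

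The result then carries forward. Study 2, Study Design, states that "only those items retained after extensive psychometric analyses will be used in the study 2 questionnaire". The first objective of study 2 (Objectives) reads "To estimate differences in HPV and cervical cancer screening knowledge and attitudes, beliefs, and preferences regarding HPV testing between women who are adequately screened", the other side of the comparison being the underscreened group. Study 2, Data Analysis, plans means and proportions for scale items, then t tests and chi-square tests "to estimate the differences between adequately screened women and underscreened women", with Cohen d and Cohen h as effect sizes.

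On language, study 1 was administered "to a national sample of Canadian women, aged 21 to 70 years, in English and French". Under Questionnaire Revisions and Translation, "this version was translated into French by a specialized translation firm"; a native speaker on the team then checked it. Phase 1B adds seven cognitive interviews, three of them in French.

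**The concern.** A factor model that fits well in a combined sample shows that one structure describes the mixture. It does not show that women at the same level of knowledge or attitude, but from different screening groups, answer an item in the same way. A comparison of scale means needs that second property (equal loadings and equal intercepts or thresholds).

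The groups here are defined by experience with the procedure that the items concern. Under Screening History, the underscreened group includes women who have never had a Pap test. Attitude and belief items about screening may be read differently with and without that experience. If several items shift in the same direction, the scale comparison would credit to attitude or knowledge what belongs to the items. The Discussion intends to base targeted interventions on these differences.

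The retention rule as written considers difficulty range, discrimination and information only. An item that functions differently in the two groups could meet all three and pass into study 2.

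**Working it through.** **Inputs from the article.** Valid study 1 responses: 1027 of 1230 (1027/1230 = 83.49%, as stated), about half from each screening group by quota. Minimum for one factor analysis: 500. Planned valid responses in study 2: (10 × 15)/0.25 = 600, then 600/0.40 = 1500 per screening group and 3000 in all, as stated. Each knowledge scale starts from 14 items (Item Selection).

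**How small a difference will register.** With 1500 per group:
- SE of d = √(2/1500) = 0.0365
- smallest significant d (two-sided 5%, assumed) = 1.96 × 0.0365 = 0.072
- d detectable with 80% power = (1.96 + 0.84) × 0.0365 = 0.102

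**How large a spurious difference could be.** Assumptions, none from the article: 14 binary items, 2PL with discrimination 1.2, difficulties evenly spaced from −1.5 to 1.5, standard normal trait, no true group difference, and some items made harder in one group.

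One case by direct calculation, with the two middle items shifted by 0.5 logit: the expected score falls from 7.00 to 6.81, the score SD is about 3.2, and d = 0.19/3.2 = 0.06.

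Simulation gives the following. Ranges reflect simulation error and the choice of difficulties and affected items.

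| Items shifted | Spurious d | t test rejects |
|---|---|---|
| 2 of 14, 0.5 logit, same direction | 0.05 to 0.06 | 27% to 38% |
| 3 of 14, 0.5 logit, same direction | 0.07 to 0.09 | 55% to 66% |
| 3 of 14, 0.7 logit, same direction | 0.11 to 0.12 | 84% to 92% |
| 1 of 14, 0.5 logit | 0.03 | 10% |
| 1 of 14, 0.3 logit | about 0.02 | 6% to 7% |
| 2 of 14, +0.5 and −0.5 logit | 0.00 | 4% |

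Shortening raises the weight of each item: 2 of 8 items at 0.5 logit gives d of about 0.08 and 60% rejection. Seven-point attitude items were not simulated, so these sizes are illustrations.

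**Language.** Bias carried into the screening contrast is the difference in French share times the language shift. With equal shares it is 0. With a 10-point difference and an assumed 0.5 SD shift it is 0.10 × 0.5 = 0.05; with a 20-point difference it is 0.20 × 0.5 = 0.10.

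**What study 1 can support.** All responses: 1027/2, about 513 per screening group. CFA half only: 1027/4, about 257 per group, against the article's own minimum of 500. The French number is not stated; at an assumed 10% to 30% it would be 103 to 308.

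**The case against.** The strongest objection is that this argues from silence. A journal article condenses, study 1 analysis was still under way, and a fuller plan might contain invariance checks. That stands as a caution: one cannot say that the checks will not be done. But the article states its item-retention rule and its fit cutoffs explicitly, and makes the outcome binding on study 2. A rule stated that fully can fairly be judged against the use it serves.

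Second, the planned comparison is at least partly item by item. A difference in the proportion answering one item correctly is a valid description whether or not the scale is invariant. For factual true/false items, fewer correct answers among never-screened women may be the very knowledge gap sought. This stands. It confines the concern to scale scores and gives it most weight for attitudes and beliefs.

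Third, the effects are small, and the plan reports Cohen d and h, so a reader would see that. This stands in part: an effect size guards against over-reading a P value but does not reveal that its source is the items.

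A reader might infer that mixing English and French answers biases the group comparison. The documents do not support that. The bias arises only if the French share differs between screening groups, which nothing in the article indicates, although the language quota is not said to apply within group. Professional translation, a native-speaker check and iterative interviews are real, if qualitative, safeguards.

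**Conclusion.** The point holds as a gap between validation and use. The stated selection and CFA combine the screening groups, and the first objective of study 2 compares them on what was selected. The size is modest and conditional: d of about 0.05 to 0.12 if 2 to 3 of 14 items shift the same way by 0.5 to 0.7 logit, and near zero if shifts are few, small or cancel. The number, size and direction of the shifts, the item discrimination and the difficulties are all assumed.

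Two stronger readings should be resisted. One is that the group differences in study 2 will be artefacts, or that the scales are invalid; the article contains no evidence of differential functioning in any item. The other is that the multinomial models are undermined; they are run separately within each screening group and do not rest on equal scores across groups. The exception would be a comparison of their coefficients between groups.

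**What to change.** Add to study 1, Data Analysis—Objective 1: Scale Validation, a DIF test by screening group within the planned 2PL and graded response models, using all 1027 valid responses. State in advance what size counts as material, and make material DIF one input to retention alongside difficulty, discrimination and information, so that a noisy flag does not by itself remove an item needed for content.

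In study 2, with 1500 per group, repeat the DIF test and add multigroup CFA (configural, metric, scalar). Report objective 1 scale differences with and without flagged items, or on latent means with those items freed.

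Treat DIF by language as a secondary check, and tabulate language by screening group. It matters for this contrast only if the French share differs.

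Costs: some additional analysis on data already collected or planned, and possibly one or two items lost. Using all 1027 responses blurs the separation of the EFA and CFA halves for this step; confining the test to the CFA half leaves about 257 per group. Study 1 precision is therefore limited, and more so for French, whose number is not stated. The repeat in study 2 is the more reliable test.
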